### Confirmatory analysis

In terms of clinical relevance, the composite pain score is the most prominent outcome: a substantial pain reduction is mandatory for treatment efficacy. We therefore apply a hierarchical testing procedure; the number and length of pain episodes will be tested only if there is a significant difference between the treatment groups in the log area under the curve (auc) of pain intensity. These endpoints will be tested to an alpha level of 2.5%; therefore, under this hierarchical design the overall alpha level of the trial will not exceed 5%.

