## Methods/Design

### Study design

Stop-FAP is a multicenter, prospective, parallel group, randomized-controlled superiority trial for the evaluation of the efficacy of a cognitive-behavioral group intervention compared to an active control group. Study process from enrollment to follow-up is depicted in Figure 1 (Trial Flow Chart).

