### Hypotheses

Our primary hypothesis postulates that children in the IG will experience a more pronounced and sustained reduction of the frequency and intensity of abdominal pain than children in the CG.

Secondary hypotheses postulate that after treatment, children in the intervention group - compared to an active control group - will experience (i) higher improvement in health- and pain-related quality of life, (ii) a higher increase in the use of adequate pain-related coping and cognitions, and (iii) a more pronounced improvement in self-efficacy.

Additionally, we assume that children and parents with more pronounced psychosocial strain gain less from treatment than those experiencing low strain.

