### Primary analysis of the primary endpoints

An analysis of covariance will be performed in the ITT population, comparing the log area under the pain intensity curve from intervention to 12-month follow-up between the two random groups adjusted for the baseline measurements. Length of pain episodes will be analyzed analogously. Frequencies will be analyzed using a Poisson regression model.

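### The two gated tests are each fixed at 2.5% with no reuse of alpha; Holm at the same overall 5% would be uniformly more powerful (an optional efficiency gain, not an error in type I control)

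*Protocol article*

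**What the plan says.** All points are in the protocol article.

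- **Confirmatory analysis** announces the design ("We therefore apply a hierarchical testing procedure") and sets the gate: "the number and length of pain episodes will be tested only if there is a significant difference between the treatment groups" in the log AUC of pain intensity.
- The same section fixes the level, "These endpoints will be tested to an alpha level of 2.5" percent, and states the result: "under this hierarchical design the overall alpha level of the trial will not exceed 5" percent. It describes no step-down and does not pass on the alpha of a successful test.
- **Primary analysis of the primary endpoints** names the tests. Log AUC is compared by analysis of covariance. For the gated endpoints: "Length of pain episodes will be analyzed analogously" and "Frequencies will be analyzed using a Poisson regression model".
- **Hypotheses** states the primary hypothesis as a "reduction of the frequency and intensity of abdominal pain", so frequency is part of what the trial sets out to confirm.

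**The concern.** Once the gate has opened, the whole 5% is available for the two remaining hypotheses. The plan divides it into two fixed halves. If length succeeds at 2.5%, frequency is still judged at 2.5%, and the reverse. A p-value between 2.5% and 5% for the second endpoint then counts as a failure, although the error limit that the plan sets itself would allow it to count as a success.

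At stake is the chance of confirming each gated endpoint, and of confirming both. The result on pain intensity and the overall error rate are not affected.

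**Working it through.** **Inputs**

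- From Sample size - power analysis: 56 per arm; d = 0.6 (given for the primary outcome only); 90 children in the per protocol analysis, taken as 45 per arm.
- From Confirmatory analysis: gate on log AUC, two gated tests at 2.5%, overall 5%.
- Assumed, because the article does not state them: the same d for all three endpoints; two-sided tests; gate at 5%; approximately normal test statistics that hold their nominal level; no gain from the baseline covariate; equal pairwise correlation of 0, 0.5 or 0.8 between the three statistics.
- Also run: d = 0.5, which is what the plan's f = 0.25 converts to for two equal groups (d = 2f), and d = 0.3.

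**Step 1. The plan's own figure.** 2 × 0.025 = 0.05. The stated limit reproduces. With independent tests the exact value is 1 − 0.975² = 0.0494.

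**Step 2. Does Holm behind the gate keep 5%?**

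- If the null hypothesis for log AUC is true, any false rejection requires passing the gate, so the error is at most 5%.
- If it is false, the only possible errors are in the Holm pair, which is held at 5%.

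Simulation agrees (2,000,000 runs for each of 30 settings, gate at 5% or 2.5%). The highest family-wise error was 0.0503; the simulation standard error is √(0.05 × 0.95 / 2,000,000) = 0.00015. With the gate passed and one gated null hypothesis false, the error for the remaining true one is 2.5% under the fixed split and 5.0% under Holm. The difference is the unused alpha.

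**Step 3. Power by hand, correlation 0, d = 0.6.** The mean of each statistic is 0.6 / √(2/56) = 3.175.

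- Power at 5%: Φ(3.175 − 1.960) = 0.888 (this is also the gate).
- Power at 2.5%: Φ(3.175 − 2.241) = 0.825.
- Per endpoint, fixed split: 0.888 × 0.825 = 0.73.
- Per endpoint, Holm: 0.888 × [0.825 + (0.888 − 0.825) × 0.825] = 0.78.
- Both, fixed split: 0.888 × 0.825² = 0.60.
- Both, Holm: 0.888 × [0.888² − (0.888 − 0.825)²] = 0.70.
- At least one, either method: 0.888 × [1 − (1 − 0.825)²] = 0.86.

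**Step 4. Simulated power, including the gate (fixed split → Holm)**

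| Per arm, d | Correlation | Per endpoint | Both | At least one |
|---|---|---|---|---|
| 56, 0.6 | 0 | 73.2% → 77.8% | 60.4% → 69.6% | 86.1%, same |
| 56, 0.6 | 0.5 | 76.4% → 80.0% | 68.2% → 75.4% | 84.6%, same |
| 56, 0.6 | 0.8 | 79.5% → 82.4% | 74.4% → 80.2% | 84.5%, same |
| 56, 0.5 | 0.5 | 55.9% → 60.1% | 45.2% → 53.5% | 66.6%, same |
| 45, 0.6 | 0.5 | 64.3% → 68.4% | 54.1% → 62.4% | 74.4%, same |
| 56, 0.3 | 0.5 | 15.7% → 17.6% | 9.2% → 12.9% | 22.2%, same |

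At least one cannot change, because Holm's first step is also at 2.5%. All three endpoints come from the same pain diary, so zero correlation is an outer case and the gains at 0.5 to 0.8 are the more relevant ones.

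**The case against.** The strongest defence is that nothing here is wrong. A gate followed by a Bonferroni split is a standard, prespecified, conservative procedure, and it delivers the 5% that it promises. The decisive test is the gate, which the change does not touch. The gain is a few points, it rests on effects and correlations that the documents do not give for these two endpoints, and matching confidence intervals become less simple than fixed 97.5% intervals. All of this stands, and it limits the point to an efficiency suggestion. It does not give a reason to prefer the fixed split for testing, because that split can only reject less often.

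Three stronger readings that a reader might infer are not supported:

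- **That the gate itself is tested at 2.5% and loses power.** The words on the 2.5% level follow directly on the number and length of episodes, and 2 × 2.5% gives the stated 5%. Losses computed for a 2.5% gate therefore carry no weight.
- **That episode length has no place among the confirmatory endpoints.** The Hypotheses section names only frequency and intensity. But Primary outcome measure derives pain duration as well as frequency from the diary, and the section on the primary endpoints includes length. Moving length to the secondary outcomes would be a choice of scope, not a correction.
- **That the gain is larger.** Assuming 80% power per gated endpoint and leaving out the gate gives 71% to 78% per endpoint and 51% to 63% for both, under independence. The documents state no such power, and these tests are run only after the gate.

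**Conclusion.** The point holds as an optional improvement. The control of type I error is valid as written. At d = 0.6 and 56 per arm, the fixed split gives up about 3 to 5 points of power per gated endpoint and about 6 to 9 points for winning both. At d = 0.3 with 56 per arm this shrinks to about 1 to 2 points per endpoint and 2 to 5 for both. The chance of winning at least one is the same under either procedure.

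The direction does not depend on the assumptions: each rejection under the fixed split is also a Holm rejection, for any effect size, correlation or sidedness. The size does depend on them. Whether the Poisson test for frequency holds its nominal level is a separate question that bears on both procedures.

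**What to change.** In Confirmatory analysis, replace the sentence on the 2.5% level with wording such as: log AUC of pain intensity is tested at two-sided 5%; if it is significant, the number and length of pain episodes are tested by Holm's procedure at an overall two-sided 5%, the smaller p-value against 2.5% and, if that is significant, the other against 5%. Length stays a confirmatory endpoint.

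The cost is one sentence. No further children or data are needed, and the family-wise error stays at or below 5%. The one drawback is in reporting: either accept that simultaneous intervals matching Holm are less simple, or report 97.5% intervals and say that they may not mirror the Holm decision for the second endpoint. The article describes the trial as recruiting, so the change should be dated and recorded before unblinding.

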### Analysis of secondary outcomes

Further, we will analyze primary and secondary outcome measures using a mixed model, adjusting for the therapist (random effect) and baseline measures (including age, gender, duration of illness, age at onset and the baseline measure of the outcome of interest).

### Exploratory analyses

We will also explore subscales of the outcome measures to see if there are indicators of treatment effects within these subscales.

In further exploratory analyses, we will include other baseline predictors in the model and explore their potential effect modification; moreover the effect of time-varying predictors will also be investigated. In a sensitivity analysis, we will explore the effect of missing values using various imputing methods (best and worst observation carried forward, last observation carried forward, full-information maximum likelihood and multiple imputation).

### Descriptive analysis

All available data will be analyzed descriptively for each intervention group. Differences in baseline variables will be analyzed by appropriate tests (for example, the Chi squared test, Kruskal-Wallis test, or analyses of variance) in pairwise comparisons between the two treatment groups.

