### Sample size - power analysis

The calculations rely on the high effect size of our primary outcome (d = 1.09 for the composite pain score; see [21, 22]) and correlation among repeated measures 0.8 (see [20–22]). Since our recent single-site study included a 3-month follow-up and a waiting list control group (instead of an active control group [21, 22]), power analysis for the primary outcome is based conservatively on a medium effect size (f = 0.25; d = 0.6). Independent variables are intervention (2), gender (2), age (2) and site of intervention (5), forming a total of 2^3^*5 = 40 groups.

In the study centers, n = 450 children will be assessed for eligibility and a total number of n = 112 children will be allocated to the trial (n = 56 in IG, n = 56 in CG). We assume a drop-out rate of 20% [cf. 18], resulting n = 112 children to be analyzed in the intention-to-treat analysis (ITT) and n = 90 children for the per protocol analysis (PPA).

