### Randomization

Allocation sequences are generated centrally at the Institute of Epidemiology at University Clinic of Hamburg-Eppendorf (KW). It will be mutually randomized in IG and CG with a 1:1 ratio. Each patient’s position on allocation sequence is defined by computer-generated random-numbers and the date of informed consent (chronologically sorted).

As groups are assigned parallel and the interventions are to be carried out mutually, blocking is dependent on the group sizes. Block sizes range between 6 and 16 patients. The total number of each block is dependent on the total number of groups to be trained. As in this trial, a maximum of 25 groups are to be trained; the number of blocks of 6 and 8 patients is restricted to five each.

The randomization procedure, in order to prevent selection bias, occurs centrally at the University of Potsdam by a person not involved in the intervention process and data analysis. We realize a stratified (according to center) block randomization. Randomization and allocation to interventions occur after assessment of pre-data and before the interventions start. Results of randomization will be provided directly only to the trainers via email (allocation concealment). Each center has to realize four different groups; at the first block of interventions, the trainer may choose the trial arm (IG versus CG); in the second block, the trainers have to change the trial arm.

The effectiveness of the randomization is evaluated post-hoc by descriptive statistical comparisons between IG and CG in known and presumed baseline predictors of treatment success (for example, pain history of the parents and socio-economic status) and relevant sociodemographic data (age and sex).

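### Baseline significance tests cannot show that randomisation worked; prespecify the named predictors in the primary ANCOVA instead

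*Protocol article*

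**What the plan says.** Four parts of the protocol article bear on this.

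- **Randomization** gives the purpose of the baseline comparison: "The effectiveness of the randomization is evaluated post-hoc by descriptive statistical comparisons between IG and CG in known and presumed baseline predictors of treatment success". The variables follow in the same sentence: "baseline predictors of treatment success (for example, pain history of the parents and socio-economic status) and relevant sociodemographic data (age and sex". Parental pain history and socio-economic status are thus given as examples of predictors, and age and sex as sociodemographic data.
- **Descriptive analysis** gives the method: "Differences in baseline variables will be analyzed by appropriate tests (for example, the Chi squared test, Kruskal-Wallis test, or analyses of variance". No significance level, threshold or consequence is stated.
- **Primary analysis of the primary endpoints** defines the confirmatory ANCOVA as "comparing the log area under the pain intensity curve from intervention to 12-month follow-up between the two random groups adjusted for the baseline measurements". The baseline measurements are not itemised.
- **Analysis of secondary outcomes** re-analyses the primary outcome in a mixed model with a therapist random effect, age, gender, duration of illness, age at onset and the baseline value. **Exploratory analyses** brings in further baseline predictors without naming them.

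**Sample size - power analysis** also lists gender, age and site with intervention as independent variables.

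**The concern.** There are two linked weaknesses.

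First, the comparisons are given an inferential job that they cannot do. A baseline test has as its null hypothesis that the arms were drawn from the same population. Correct central randomisation makes that true by construction, so a small p-value shows only that chance occurred, and a large one does not show that the arms are alike. What matters for the treatment estimate is the size of the imbalance and how strongly the variable predicts pain. The p-value measures neither.

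Second, the part of the plan that could deal with chance imbalance, the confirmatory model, does not name the variables that the protocol itself considers worth checking. Age and gender enter a supporting model of the same outcome and the sample-size reasoning, but are not named in the primary ANCOVA. Parental pain history and socio-economic status are named in no model. At stake are some precision in the primary comparison and protection of the realised estimate against a chance imbalance. The validity of the primary test is not at stake.

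**Working it through.** **Inputs from the protocol.** Sample size: "n = 112 children will be allocated to the trial (n = 56 in IG, n = 56 in CG". Planning effect: "power analysis for the primary outcome is based conservatively on a medium effect size (f = 0.25; d = 0.6". Confirmatory alpha: 2.5% per endpoint (Confirmatory analysis), sidedness not stated.

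**Assumptions.** Two-sided 5% for the baseline tests, since no level is given. Standardised effect d = 0.5, because f = 0.25 with two equal groups gives d = 2f = 0.5. (The stated d = 0.6 does not match that f, which is a separate point.) The effect is taken on the scale of the outcome after adjustment for baseline pain. Clustering by training group is ignored.

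**The plan's own figure.** 112 × (1 − 0.20) = 89.6, which agrees with the stated 90 for the per-protocol analysis. The article states no power and no operating characteristic for the baseline tests.

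**1. False alarms under sound randomisation.** For k independent tests at 5%, P(at least one p < 0.05) = 1 − 0.95^k.
- k = 4 (the variables named): 1 − 0.95⁴ = 18.5%.
- k = 10 (for illustration): 1 − 0.95¹⁰ = 40.1%.

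**2. What a non-significant result allows.** For a continuous variable, the standard error of the difference in SD units is √(2/56) = 0.189. The largest non-significant observed difference is t(0.975; 110) × 0.189 = 1.982 × 0.189 = 0.37 SD.

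**3. Effect of an imbalance on the estimate.** If a predictor has correlation r with the outcome after baseline-pain adjustment, and the arms differ on it by Δ SD, the estimate omitting it shifts by about r × Δ. At Δ = 0.37:
- r = 0.2: 0.07 SD
- r = 0.3: 0.11 SD
- r = 0.4: 0.15 SD

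Including the predictor removes this shift.

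**4. Gain in power from adjustment.** The residual SD shrinks by √(1 − r²), so the effective d is 0.5/√(1 − r²). Power is from the two-sample t-test with 56 per arm, with r as the joint residual correlation of the added predictors.

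| r | effective d | power, two-sided 5% | power, two-sided 2.5% |
|---|---|---|---|
| 0 | 0.500 | 75% | 65% |
| 0.2 | 0.510 | 76% | 67% |
| 0.3 | 0.524 | 79% | 69% |
| 0.4 | 0.546 | 82% | 73% |

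If the 2.5% is meant one-sided, the 5% column applies.

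**5. Cost of the extra terms.** The baseline-pain-only model leaves 112 − 3 = 109 residual degrees of freedom. Four predictors (one term each) and four for centre leave 101. Chance correlation of four predictors with treatment inflates the variance of the treatment effect on average by (112 − 3)/(112 − 4 − 3) = 109/105 = 1.038. Centre is stratified and adds almost nothing to this. With worthless predictors the effective d is 0.5/√1.038 = 0.491, and power is 73% instead of 75% (63% instead of 65% at 2.5%). Net of this cost, power at two-sided 5% is about 75%, 77% and 80% for r = 0.2, 0.3 and 0.4. The break-even is therefore near r = 0.2.

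**The case against.** The strongest reply is that nothing in the trial turns on these tests. The Randomization section calls the comparisons descriptive, and the tests stand under a descriptive heading. No pass/fail rule is given, and no covariate is chosen from the results. That is correct. A reader might infer that the plan declares the arms comparable when p-values are large, but the document does not say so. What remains is that it gives the comparisons the purpose of evaluating randomisation, and they cannot serve it.

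A reader might also compute the power of a t-test and conclude that these tests would overlook a 0.5-SD imbalance about a quarter of the time. This does not hold. An imbalance of 0.5 SD actually present between arms of 56 gives t = 0.5/0.189 = 2.65, p = 0.009, and is flagged. The quarter is the type II error against a true population difference, which sound randomisation excludes.

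Nor does the omission of predictors invalidate the primary ANCOVA. Across randomisations it is unbiased and holds its level, and the shift in step 3 arises only in trials where the imbalance happens to occur. Under sound randomisation an observed gap of 0.25 to 0.37 SD on a given variable has probability 2 × (0.093 − 0.025), about 14%.

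Finally, the mixed model already adjusts for age and gender, and a covariate list may be completed in an analysis plan not shown here. Both points limit the weight of the concern. They do not explain why the confirmatory model, as stated, is less fully specified than the supporting model of the same outcome.

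**Conclusion.** The point holds as a modest, inexpensive improvement. Baseline significance tests cannot establish the effectiveness of randomisation: four independent variables produce at least one false alarm in 18.5% of sound trials, and observed gaps of up to about 0.37 SD pass unflagged, both at an assumed 5% level. Dropping them is good practice but changes no primary result.

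The useful part is the primary model. Prespecifying the named predictors raises power from 75% to 76–82% at two-sided 5%, or from 65% to 67–73% at 2.5%, and removes the bias conditional on a chance imbalance. These figures rest on d = 0.5, 56 analysed per arm and residual correlations of 0.2 to 0.4, none of which the protocol supports with data for these predictors. Allowing for the cost of the extra terms, the power gain disappears near 0.2 and is about 2 to 5 points at 0.3 to 0.4. The documents do not support a claim that the primary analysis is biased or its error rate wrong.

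**What to change.** 1. **Primary analysis of the primary endpoints.** Itemise the covariates: baseline pain, age, sex, parental pain history, socio-economic status and centre (the stratification factor). Fix their coding in advance and include them whatever the baseline table shows. Keep the model adjusted for baseline pain only as a sensitivity analysis.
2. **Descriptive analysis** (minor). Replace the tests with means and SDs or counts per arm, and standardised differences.
3. **Randomization** (minor). Remove the statement that baseline comparisons evaluate the effectiveness of randomisation. Judge its conduct from the allocation log: whether the sequence was followed, and whether block and centre counts are as planned.

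**Cost.** About four degrees of freedom for the predictors and four for centre, out of 109, and up to about 2 points of power if the predictors are unrelated to outcome. No new data should be needed: family pain history is collected at screening, and the Randomization section implies that socio-economic status is available. Because the trial is recruiting, the change to the confirmatory model should be made as a dated amendment before unblinding.

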### Monitoring and data management

We concentrate our quality assurance and monitoring on two aspects: standardization of recruitment and data collection, and standardization/fidelity of intervention.

#### Monitoring

Regular monitoring on the spot includes supervision of study nurses, control of protocol adherence, adherence to intervention protocol and data quality assurance.

In addition, for coordinating the trial across the study centers, there will be, in addition to the above mentioned monitoring on the spot, principle investigator (PI) and site investigator conference calls for cross-site reliability, standardization and monitoring by checking compliance to the protocol, inclusion/exclusion criteria and progress of the intervention (individually, every month and for all trial sites and the coordinator, every 3 months). For assuring the quality of treatment, the therapist and evaluator will be in contact via conference calls as well.

Follow-up assessment is monitored by the principle investigator. Audits can be held by the funding organization at any time and the process will be independent from the sponsor and the investigators.

